#### Sample size calculations

The sample size calculation is based on a minimum clinically important difference for the primary outcome measure (SGRQ) of 4.0 [52], between subject standard deviation in SGRQ of 13 in a similar population [54], intra-cluster correlation coefficient of 0.01, and a resultant design effect of 1.09 for a cluster size of 10. With this design effect, a sample size of 200 patients completing each arm will provide >80% power to detect a difference of 4 or greater in SGRQ (calculations in PASS software). Forty practices will each invite 300 patients to attend a case-finding appointment, and within each practice this is expected to produce 12 patients with a new diagnosis of COPD; loss to follow-up of 20% by 12 months has been assumed. The projected recruitment rate is derived from the response rate to invitation (25%), and the yield of new diagnoses (21%) in our recently completed case-finding project [10].

This sample size will also confer 90% power to identify a doubling of the expected rate of correct inhaler use (from 20% to 40%) at a significance level of 5% (based on an ICCC of 0.1, and design effect of 2.1).

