## Background

Chronic obstructive pulmonary disease (COPD) is a leading cause of morbidity and mortality [1], ranked globally in 2002 as the fifth leading cause of death [2] and the seventh leading cause of disease burden after ischaemic heart disease and stroke. In Australia, COPD is the fourth leading cause of death for males (4.2% of all deaths) and the sixth leading cause of death for women (3.3% of all deaths); it is also a contributory cause of death in many patients with coronary heart disease or cancer [3]. In the Burden Of Obstructive Lung Disease survey (BOLD), the prevalence of airflow limitation (GOLD Stage II or higher) in Australians aged ≥40 years was 10.8% [4], whereas the prevalence of doctor-diagnosed COPD in the same population was 5.9% [5].

Clinically, COPD is characterised by airflow limitation that is not fully reversible, and is associated with an enhanced chronic inflammatory response to noxious particles or gases [6]. Patients typically present with breathlessness, cough, and sputum production. The most important cause in developed countries is cigarette smoking, and up to 50% of smokers may eventually develop clinically significant COPD [7].

Even mild to moderate COPD is associated with impaired health status [8]. Patients with COPD have increased healthcare utilisation before diagnosis, raising the possibility that earlier diagnosis may allow more rational and directed use of healthcare resources [9]. The feasibility of a COPD case-finding approach has been established. For example, in an Australian study in 2007, 20% of patients identified as being at risk of COPD responded to invitations to be screened and of these 20% had a new diagnosis of COPD on spirometric criteria [10]. This is similar to findings from primary care studies in other countries [11-13]. For diagnosis of COPD, spirometry is required [6], and standards have been developed for the performance of spirometry in primary care [14]. Practice nurses can feasibly and successfully undertake spirometry [13,15]; as for other health professionals, approximately six hours of training are required [16].

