#### Reimbursement

The project will provide the following support to participating practices:

1. Intervention and control practices: Reimbursement for the practice nurse attendance at the COPD diagnosis and spirometry workshop (AUD270); payment for the practice nurse to undertake the medical record search (AUD500); reimbursement for practice nurse time for case-finding consultations (AUD38.50 for each appointment, for up to 60 patients per practice); continuing professional development points for workshop attendance.

2. Intervention group: reimbursement for practice nurse attendance at the COPD team management workshop (AUD270); reimbursement for GP attendance at the team management workshop (AUD450); category two continuing professional development points for GPs.

Once a diagnosis of COPD is made, any medical or practice nurse consultations that are required for clinical management may be funded through normal practice processes.

Small gifts (food baskets) will be provided to practice reception staff as thanks for their assistance in making follow-up telephone calls.

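### The recruitment projection does not follow from its stated inputs: 300 invitations at 25% and 21% give 15.75 diagnoses per practice, not 12, and 12 with 20% loss gives 192 completers per arm, not 200

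*Protocol article*

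**What the plan says.** The protocol article, under Sample size calculations, sets a target of 200 patients completing in each arm. It uses an SGRQ difference of 4, a standard deviation of 13, an intra-cluster correlation of 0.01 and a cluster size of 10, with a design effect of 1.09.

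On recruitment, the same section says "Forty practices will each invite 300 patients to attend a case-finding appointment". Its forecast from those invitations is that "within each practice this is expected to produce 12 patients with a new diagnosis of COPD; loss to follow-up of 20% by 12 months", the last figure being an assumption. It gives the basis for the forecast as the "response rate to invitation (25%), and the yield of new diagnoses (21%) in our recently completed case-finding project [10"].

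The Background cites the same reference for an Australian study and reports that "20% of patients identified as being at risk of COPD responded to invitations to be screened and of these 20% had a new diagnosis", made by spirometry.

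Under Reimbursement, practices are paid for case-finding appointments "for up to 60 patients per practice".

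**The concern.** A reader should be able to get from invitations to diagnoses, and from diagnoses to completers, using the figures printed. Neither step works. The two quoted rates give more diagnoses than the 12 stated, and the 12 gives fewer completers than the 200 on which power is calculated. In addition, one cited project appears in two sections with different rates, and only one of the pairs gives 12.

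What is at stake is the projection. Depending on which printed figures are used, the trial expects 192, 200 or 252 completers per arm. That matters to anyone judging whether 300 invitations per practice are enough, or comparing actual recruitment with the plan.

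**Working it through.** **Inputs.** From Sample size calculations: 40 practices, 300 invitations each, 25% response, 21% yield, 12 diagnoses per practice, 20% loss by 12 months, 200 completers per arm, cluster size 10, difference 4, SD 13, intra-cluster correlation 0.01. From the Background: 20% response and 20% yield. Two assumptions are mine: 20 practices per arm (implied by 200 completers per arm at 10 per practice), and a two-sided 5% test for SGRQ (the section states 5% only for the inhaler outcome).

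**1. The plan's power figure.**
- Design effect = 1 + (10 − 1) × 0.01 = 1.09, as stated.
- Power = Φ(4 / (13 × √(2 × DE / n)) − 1.96).
- With n = 200 and DE = 1.09, the standard error is 13 × √(2 × 1.09 / 200) = 1.357. The ratio is 4 / 1.357 = 2.947, and Φ(0.987) = 83.8%.

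The claim of more than 80% power reproduces.

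**2. Invitations to diagnoses.**
- Rates in the sample size section: 300 × 0.25 × 0.21 = 15.75 per practice, against 12 stated. The computed figure is 31% higher (15.75 / 12 = 1.31), too much for rounding.
- Rates in the Background: 300 × 0.20 × 0.20 = 12 exactly.

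**3. Diagnoses to completers.**
- From 12: 12 × 0.80 = 9.6 per practice, and × 20 = 192 per arm. This is 8 patients, or 4%, below 200.
- From 15.75: 15.75 × 0.80 = 12.6 per practice, and × 20 = 252 per arm.
- Backwards from 200: 200 / 0.80 = 250 enrolled per arm, or 12.5 per practice.

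**4. Can another reading rescue the figures?**
- If 12 meant completers, 15.75 × 0.80 = 12.6 would be near it. But the text calls the 12 new diagnoses, and the powered cluster size is 10.
- Inflating by 1 + 0.20 instead of dividing by 1 − 0.20 gives 10 × 1.2 = 12. That links 12 to 200 by a wrong adjustment for loss, and leaves step 2 open.
- Sixty visits at a 21% yield give 60 × 0.21 = 12.6 diagnoses and 12.6 × 0.80 × 20 = 201.6 completers per arm. But the section does not bring 60 visits into the calculation.

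**5. Effect on primary power.** The cluster size is completers per arm divided by 20.

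| Completers per arm | Per practice | Design effect | Power (normal) | Power (t, 38 df) |
|---|---|---|---|---|
| 192 | 9.6 | 1.086 | 82.5% | 80.5% |
| 200 | 10 | 1.09 | 83.8% | 81.9% |
| 252 | 12.6 | 1.116 | 90.5% | 89.0% |

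The last column uses the noncentral t distribution with 40 − 2 = 38 degrees of freedom. About 181 completers per arm are needed for 80% power by the normal formula at a design effect of 1.09.

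**The case against.** The best defence is that the sample size itself is sound. The 200 per arm follows from the difference, SD, correlation and cluster size, and only the recruitment forecast is loose. This stands, and it limits the point to the forecast.

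The defence can also explain each gap separately. The 9.6 may have been rounded to 10. Responding is not the same as attending, because the recruitment procedure puts an appointment and consent between the reply and spirometry, so 15.75 could be a ceiling and 12 a cautious forecast. The Background rate is among patients identified as at risk, whereas the other is a response to invitation; if not all those identified were invited, both could be true, and 20% against 21% could be rounding. All of this is possible, but none of it is stated. The section says the forecast is derived from 25% and 21%, and mentions no allowance for non-attendance. No single one of these readings closes both steps.

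A reader might infer more than the article supports:

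- **That the trial is underpowered.** It is not on the stated assumptions: power is above 80% at 192.
- **That the 12 was computed from 20% × 20%.** The match is exact, but the article does not say so, and 60 × 0.20 and 10 × 1.2 also give 12.
- **That the payment cap contradicts the plan.** A 25% response would be 75 replies per practice, but the 60 in the Reimbursement section limits what is paid for, not how many patients may attend or enrol.
- **That recruitment cannot be monitored.** The section does give targets for invitations, diagnoses and completers; they just do not agree with each other.

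**Conclusion.** The point holds as an error in the recruitment figures. The quoted rates give 15.75 diagnoses per practice instead of 12, and the quoted 12 gives 192 completers per arm instead of 200. The two errors run in opposite directions: the stated rates overshoot the target by 52 per arm (252 − 200) and the stated 12 undershoots it by 8. The primary power claim survives in each case.

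The two pairs of rates attributed to one source need reconciling. Which pair is right, or whether they have different denominators, cannot be settled from the article.

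The arithmetic on diagnoses needs no assumption beyond the printed figures. The per-arm counts assume 20 practices in each arm, and the power figures also assume a two-sided 5% test.

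**What to change.** Restate one consistent chain in Sample size calculations:

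- either give rates that produce 12 diagnoses per practice, and carry them through to 9.6 completers per practice, 192 per arm, a design effect of 1.086 and power of about 82%;
- or keep 25% and 21%, and state 15.75 diagnoses per practice and 252 completers per arm. If attendance is expected to fall below response, state that allowance and reduce both figures accordingly.

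Quote the earlier case-finding project with the same rates in the Background and in Sample size calculations, or state the denominator of each rate.

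The cost is a few sentences. The number of practices, the number of invitations, the payment cap, the enrolment rules and the analysis all stay as they are.

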## Discussion

There is substantial evidence that COPD is under-diagnosed in the community, and that even once a diagnosis of COPD is made, many patients are not managed according to evidence-based guidelines. By the time the diagnosis is made, COPD is often far-advanced, limiting the benefit that could potentially be achieved through early intervention with strategies such as smoking cessation, dietary advice, and increased exercise. This study will use proven case-finding methods in an at-risk population to identify new patients with COPD, followed by a pragmatic cluster randomised study design to test a novel intervention designed to improve the implementation of evidence-based guidelines for newly-diagnosed COPD. Practice nurses and GPs will be trained in practical strategies for assessing and managing COPD, and in working as a team in managing patients with chronic diseases. Elements of the intervention have been piloted and found to be feasible. The impact of this team-based approach to COPD management on quality of life will be compared with usual care using a widely used and validated tool (SGRQ). Other outcome measures will evaluate the concordance of patient management with evidence-based guidelines for management of COPD, using instruments with demonstrated validity and reliability, which are congruent with the recommendations of the ERS/ATS Task Force on COPD trials [56]. In addition, the acceptability of the team management approach to GPs and practice nurses, and barriers and facilitators to its implementation, will be evaluated with structured interviews at study end.

This study targets COPD patients in general practice where the contact with potential patients with mild and moderate COPD is greatest, and where improved care has the potential for substantial health benefit. Because COPD is a major contributor to the burden of disease in countries such as Australia, improved care is of great public health significance. If successful, the trial will provide a model for care of COPD patients in the community that is feasible and sustainable. Publication of the results of the trial will influence policy and practice on how care for COPD is provided at a national and international level.

### Sustainability of the intervention

In this pragmatic study, the intervention deliberately makes use of and augments existing practice structures, staffing, and approaches to chronic disease management. While there is potential for nurses to undertake advanced practice in primary care, this study will not require practice nurses to work at an advanced practice level. For this study, the role of the practice nurse is focussed on patient assessment; counselling; education; and liaison with medical and allied health colleagues, using expertise that forms part of the skills base of registered nurses. The intervention is thus potentially generalizable and easily transferable.

## Abbreviations

BOLD, Burden of Obstructive Lung Disease; CAT, COPD Assessment Test; CDQ, COPD diagnostic questionnaire; COPD, Chronic obstructive pulmonary disease; FEV_1_, Forced expiratory volume in one second; GOLD, Global Initiative for Chronic Obstructive Pulmonary Disease; GP, General practitioner; PELICAN, Primary care EarLy Intervention for Copd mANagement; PN, Practice nurse; SGRQ, St George’s Respiratory Questionnaire.
